## Abstract

**Background:**

Due to early detection and advances in treatment, the number of women surviving breast cancer is increasing. Whilst there are many positive aspects of improved survival, breast cancer survival is associated with many long-term health and psychosocial sequelae. Engaging in regular physical activity post-diagnosis can reduce this burden. Despite this evidence, the majority of breast cancer survivors do not engage in regular physical activity. The challenge is to provide breast cancer survivors with appealing and effective physical activity support in a sustainable and cost-effective way. This article describes the protocol for the *Move More for Life* Study, which aims to assess the relative efficacy of two promising theory-based, print interventions designed to promote regular physical activity amongst breast cancer survivors.

**Method and design:**

Breast cancer survivors were recruited from across Australia. Participants will be randomised into one of three groups: (1) A tailored-print intervention group, (2) a targeted-print intervention group, or (3) a standard recommendation control group. Participants in the tailored-print intervention group will receive 3 tailored newsletters in the mail over a three month period. Participants in the targeted-print group will receive a previously developed physical activity guidebook designed specifically for breast cancer survivors immediately after baseline. Participants in the standard recommendation control will receive a brochure detailing the physical activity guidelines for Australian adults. All participants will be assessed at baseline, and at 4 and 10 months post-baseline. Intervention efficacy for changing the primary outcomes (mins/wk aerobic physical activity; sessions/exercises per week resistance physical activity) and secondary outcomes (steps per day, health-related quality life, compliance with physical activity guidelines, fatigue) will be assessed. Mediation and moderation analyses will also be conducted.

**Discussion:**

Given the growing number of cancer survivors, distance-based behaviour change programs addressing physical activity have the potential to make a significant public health impact.

**Trial registration:**

Australian New Zealand Clinical Trials Registry (ANZCTR) identifier: ACTRN12611001061921

## Background

Due to earlier detection and advances in treatment, more and more women are surviving breast cancer each year
[1]. Whilst improved survival is duly welcomed, breast cancer survivors are faced with both short and long-term health and psychosocial sequelae
[2], including fatigue, reductions in physical and cognitive functioning, reductions in bone health, lymphedema, weight gain and mood disturbances
[3-6]. Compared to the general (non-cancer) population, breast cancer survivors are at an increased risk of co-morbid chronic conditions and death from both cancer and non-cancer causes
[7]. As such, there is a growing need for effective cancer recovery services that can help to improve the quality of life of breast cancer survivors and negate the associated health burdens and risks
[8].

One promising cancer recovery strategy is the promotion of regular physical activity (PA)
[9,10]. Evidence from health outcome trials suggests that regular PA can address both the psychological and physiological burdens presented after breast cancer diagnosis and treatment
[11,12]. Furthermore, observational research suggests that regular PA may also have an impact on survival, with breast cancer survivors who are active after treatment having a lower risk of cancer recurrence, co-morbidities and death from all causes compared to those who are less active, regardless of cancer stage
[13-15]. In recognition of these benefits, detailed exercise prescription guidelines for cancer survivors have been published by professional bodies in both Australia and North America
[9,10,16].

There is also new evidence that addressing the pattern of activity is important, with unique metabolic consequences associated with prolonged sedentary behaviour, regardless of total activity time
[15,17]. Despite this evidence, the majority of breast cancer survivors are not sufficiently active for health
[17,18] and efforts to encourage regular PA and reductions in sitting time are not a routine part of the cancer treatment or rehabilitation process
[19-22].

Whilst over 70 PA intervention studies have been conducted with cancer survivors, the majority have been atheoretical face-to-face programs conducted during the treatment phase
[23-26]. Whilst these interventions have been efficacious in improving important outcomes for cancer survivors, there is a need for more sustainable, less resource intensive approaches that can support survivors beyond the initial treatment phase
[27-29]. Such programs should be grounded in behaviour change theory, and address the unique determinants of PA adoption and maintenance in the post-treatment breast cancer population
[30,31].

The purpose of this study is to evaluate the relative efficacy of two promising distance-based approaches (targeted and tailored print interventions) for promoting PA among post-treatment breast cancer survivors compared to a standard recommendation control group. In targeted-print interventions, irrelevant information is reduced by providing individuals with materials targeted to a particular subgroup they belong to (e.g., breast cancer survivors)
[32]. In tailored-print interventions, computer technology is utilised to provide individuals with personalised advice based on information specific to them (derived from individual assessment)
[32]. Both approaches have been put forth as low-cost, evidence-based alternatives to resource intensive face-to-face programs
[32,33], but little information exists about the relative efficacy and the cost/benefit of these approaches in the physical activity domain.

Some theories of information processing, such as The Elaboration Likelihood Model
[34], suggest that people are more likely to process information in a way that is conducive to behaviour change, if it is personally relevant to them. Based on this model, we hypothesise that individuals randomised into either the targeted or tailored print groups will experience significantly greater improvements at each timepoint on all primary and secondary outcomes compared to the standard recommendation control group. Furthermore, given the greater level of personalisation of materials in the tailored-print condition, we expect participants in the tailored-print group to experience greater improvements across PA outcomes compared to participants in the targeted-print group. This hypothesis relies on the assumption that breast cancer survivors are a somewhat heterogeneous group in terms of determinants (i.e., demographics, social-cognitive and ecological factors) of PA behaviour change.

## Methods

### Design

This study is a nationally-based, three-arm randomised controlled trial (RCT), testing the relative efficacy of two distance-based PA interventions (tailored and targeted print) compared to a standard recommendation control group. Participants will complete data collection at baseline, 4 months and 10 months. Ethics approval was obtained from the University of Newcastle Human Research Ethics Committee (H-2010-11-3). The RE-AIM framework
[35] will serve to guide the dissemination of this program in terms of adoption, implementation and maintenance. The conduct and reporting of this study will adhere to the Consolidating Standards of Reporting Clinical Trials (CONSORT) guidelines
[36] and to the Reporting Standards for Studies of Tailored Interventions
[37]. The study flow chart is presented in Figure
1 (note: recruitment for this study is complete). 

**Figure 1 F1:**
[figure not shown]
Study flow chart.

### Participants

#### Selection criteria

Female breast cancer survivors who are over the age of 18 and who have finished “active” cancer treatment (defined as surgery, chemotherapy and/or radiotherapy), who can read and write in English were eligible to participate in the study. All potential participants were required to complete a physical activity readiness questionnaire (PAR-Q;
[38]), to screen participants and identify those requiring review from their doctor prior to study enrolment.

#### Recruitment

Participants were recruited using convenience sampling methods from a range of sources across Australia. Specifically, this involved (1) asking organisations (e.g., The Breast Cancer Network Australia, The Cancer Council, YWCA Encore) and health professionals (e.g., breast care nurses) with direct contact with breast cancer survivors to disseminate information about the study on behalf of the research team; (2) promoting the study at events potentially relevant to eligible participants (e.g. breast cancer forums); and (3) snowballing recruitment (inviting participants to pass on study information to potentially eligible friends and acquaintances).

### Randomisation

The randomisation sequence will be generated by a statistician (PM) using SAS 9.2 statistical software. An equal number of participants will be randomised to each group (1:1:1) using a randomised block design, with a block size of six, to ensure the study groups are balanced
[39,40].

Participants, identified only by their ID number, will be randomised by an administrative staff member into groups upon receipt of their baseline survey. All project team members will be blinded to this process and participant details will remain de-identified until participant allocation is completed. Participant blinding is not possible due to the difference in delivery schedule of the two interventions.

### Statistical power and sample size

The study’s primary analysis will be the comparison of self-reported PA behaviour (i.e. mins/week of aerobic exercise and sessions/week of resistance training) between the three groups, from baseline to the 4 month time-point. Assuming a small-moderate correlation (r = 0.4) between baseline and post-intervention, to detect a mean difference of 0.5 standard deviation between study groups (small-medium effect size) for the main dependent outcome (i.e., PA behaviour) at post-intervention
[41] the required sample size is 100 participants per group, allowing for a 20% loss to follow-up (power = 0.80; alpha = 0.01). An alpha of 0.01 was used to adjust for multiple comparisons.

As a secondary consideration, we also ensured that this sample size would be adequate to detect a clinically significant change in step counts per day (2000 steps per day
[42], standard deviation of 3500
[43]) and found that we would be adequately powered to detect meaningful changes in both self-report and objective PA outcomes.

### Outcomes

A pen-and-paper questionnaire is completed at baseline, 4 months post baseline (immediate post- tailored intervention follow-up), and 10 months post-baseline (7 month post tailored-intervention follow-up). At each of these time-points, participants will be asked to wear a pedometer for seven days and complete a step count diary.

#### Primary outcome

The primary outcome variables, minutes of PA (aerobic) per week and average number of sessions/exercises per week (resistance) will be assessed using an adapted version
[44] of the validated Godin Leisure-Time Exercise Questionnaire (GLTEQ)
[45]. The adapted version will incorporate a resistance training (RT) measure
[44,46] that asks participants to report the frequency (times per week) and duration (average times per session) of resistance training activities on average over the past month. The original measure has been found to be both reliable and valid
[47].

#### Secondary outcomes

##### Step counts

Average daily step counts
[48] will be estimated based on at least three days of pedometry, which is sufficient to reliably estimate pedometer-determined PA
[49,50]. Participants will be instructed to zero the pedometer and record their accumulated steps at the end of each day for seven days, using the step count diary provided. The step count diary will also be used to record instances where the pedometer was intentionally removed (e.g. swimming) or when the participant forget to wear the device. Where reported, step count equivalents for non-ambulatory activities (e.g. swimming, cycling) will be calculated and added to the step count total using the method outlined by Miller et al.
[51].

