##### Tailored-print intervention

Participants randomised into this group will be mailed three Social Cognitive Theory-based
[68,69] computer-tailored newsletters over a 12 week period (6 weeks apart). Each newsletter will be four A4 pages in length and will provide advice and feedback unique to the individual that relates to key determinants of PA adoption and maintenance among breast cancer survivors (as stipulated by previous research in the field
[57,70-77] and Social Cognitive Theory
[68,78]). The advice participants receive will be tailored using information derived from individual assessments at baseline, and ‘update cards’ (assessing PA and goal setting behaviour over the last month) sent to participants (in this group only) at 4 weeks and 8 weeks post-baseline. In each case, participants will be mailed the tailored-newsletters within two weeks after the completed assessment is received (see Figure
1).

*Newsletter 1 (N1)* will include information on the Australian PA guidelines for cancer survivors (non-tailored), tailored feedback on PA behaviour (aerobic, resistance and sitting time) relative to the guidelines, information about the beneficial outcomes of PA, safety advice and an action planning activity. An activity planner and exercise illustrations (stretches and resistance training exercises) will also be included.

*Newsletter 2 (N2)* will include expert advice from a behaviour change expert (non-tailored), feedback on PA performance (aerobic, resistance and sitting time) relative to N1, a testimonial illustrating success, advice on eliciting social support and an action planning activity.

*Newsletter 3 (N3)* will include expert advice from an exercise physiologist (non-tailored), tailored feedback on PA performance (aerobic, resistance and sitting time) relative to N2 and N1, advice on restructuring the physical environment, information about available support services and an action planning activity. See Additional file
1 (Table S1) for a brief overview of how Social Cognitive Theory was operationalised to form these intervention strategies and what variables were used to tailor information.

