## Discussion

This study will test the relative efficacy of two theory-based PA behaviour change interventions. In doing so, this study will address a seminal research question in distance-based patient-centred care – is tailoring or targeting health education messages a more efficacious approach to health behaviour change in the PA domain? Furthermore, this study will be one of the first to promote a pattern of PA that addresses the metabolic consequences of unbroken sedentary behaviours and the advantages of completing both aerobic and resistance-training exercises. The limitations reported in previous research will be addressed by examining adherence after the intervention period and by utilising an objective measure of PA behaviour (i.e., pedometers). Finally, this study will add to the behaviour change literature by addressing the paucity of knowledge surrounding determinants of PA behaviour change among cancer survivors and potential mediators of intervention effects.

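### The step outcome called objective includes step equivalents converted from participant-reported swimming and cycling; unadjusted pedometer steps should be analysed separately and carry the objective claim

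*Protocol article*

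**What the plan says.** The Step counts section, under Secondary outcomes, builds the outcome from two parts.

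- **Pedometer part.** "Participants will be instructed to zero the pedometer and record their accumulated steps at the end of each day for seven days".
- **Reported part.** "The step count diary will also be used to record instances where the pedometer was intentionally removed (e.g. swimming") and occasions when the participant forgot to wear the device. Then, where such activity is reported, "step count equivalents for non-ambulatory activities (e.g. swimming, cycling) will be calculated and added to the step count total", by a cited published method.

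The article names no analysis of steps without the added part.

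Two other sections describe the role of this outcome. Statistical power and sample size concludes that the trial is "adequately powered to detect meaningful changes in both self-report and objective PA outcomes", with steps as the objective one. The Discussion says that limitations of earlier research will be addressed in part by "utilising an objective measure of PA behaviour (i.e., pedometers").

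The primary outcomes come from a questionnaire: "The study’s primary analysis will be the comparison of self-reported PA behaviour". On blinding, the Randomisation section says: "Participant blinding is not possible due to the difference in delivery schedule of the two interventions".

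**The concern.** The definition and the label do not match. An outcome that contains converted self-report is not objective in the sense in which the sample size section sets it against self-report. The mismatch matters because steps are the only outcome described that uses a device. Aerobic and resistance activity, guideline adherence, sitting time, quality of life and fatigue are all taken from questionnaires.

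Participants know what materials they received. If one arm reports swimming or cycling more fully after randomisation, the conversion turns that reporting into steps and the arms differ without any difference in movement. Adjustment for baseline, if steps are analysed in the same way as the primary outcomes, would remove stable habits of reporting. It would not remove a change in reporting that arises after randomisation. At stake is whether a difference in steps can be described as an objective effect on activity.

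**Working it through.** **1. The article's own figures.** These reproduce and are not in dispute. Inputs from Statistical power and sample size: difference 0.5 SD, r = 0.4, alpha 0.01 (taken as two-sided), power 0.80, 20% loss.

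- Primary outcome: n = 2 × (2.576 + 0.842)² × (1 − 0.4²) / 0.5² = 78.5, so 79 per group. 79 / 0.80 = 98.75, so 99, against the stated 100.
- Steps, difference 2000 and SD 3500, no baseline adjustment: n = 2 × (2.576 + 0.842)² × (3500/2000)² = 71.5, so 72 per group. 72 / 0.80 = 90, which is within 100.

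**2. The passages side by side.**

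| Section | What it fixes |
|---|---|
| Step counts | Total = pedometer count + equivalents for reported activity |
| Statistical power and sample size | Steps are the objective outcome, in contrast to self-report |
| Discussion | The pedometer is the objective measure |
| Randomisation | Participants are not blinded |

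The only step outcome defined is the combined total, so the objective label falls on a figure that is partly reported.

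**3. Illustration of size.** The documents give neither the conversion rate nor how often women swim or cycle. Both inputs here are assumptions: 100 to 200 step equivalents per minute, and a spurious difference in arm means of 15 to 30 minutes per week.

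Added steps/day = minutes per week × steps per minute / 7.

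| Minutes per week | 100 steps/min | 200 steps/min |
|---|---|---|
| 15 | 214 (11% of 2000) | 429 (21%) |
| 30 | 429 (21%) | 857 (43%) |

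**4. What that would do to a test.** Take 80 completers per arm (100 less 20%), SD 3500, two-sided alpha 0.01, no true effect and no baseline adjustment. The standard error of the difference is 3500 × √(2/80) = 553. The chance of a significant result is Φ(b/553 − 2.576) + Φ(−b/553 − 2.576), where b is the spurious difference in steps/day.

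| b | Chance of a significant result |
|---|---|
| 0 | 1% |
| 214 | 1.6% |
| 429 | 3.6% |
| 857 | 15.2% |

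The lower end is close to harmless and the upper end is not. Nothing in the documents says where the trial lies.

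**5. Power without the added part.** If the SD of 3500 applies to unadjusted steps, which the article does not say, 2000/553 − 2.576 = 1.04. That gives 85% power with 80 completers per arm at alpha 0.01.

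**The case against.** The case for the plan is a fair one, and several parts of it stand.

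- **The adjustment has a reason.** A pedometer misses swimming and cycling. The interventions promote aerobic activity in general, so unadjusted steps could lose real gains, perhaps unequally by arm. A published method is cited and is to be applied to every arm. This stands, and it is why the adjusted total should be kept. Which of the two totals should be the main definition is open to debate.
- **The daily count is itself handwritten.** Unblinded participants copy every reading into the diary, and no download from the device is described. This stands too: removing the equivalents does not make the outcome purely device-based. But copying a reading is different from reporting activity that no device registered.
- **The illustration may be generous.** The minutes are differences in arm means. If, as an assumption, 20% of women swim or cycle, a mean difference of 30 minutes per week needs each of them to over-report by 150 minutes, and 15 minutes needs 75. This stands, so the figures are not an estimate.
- **An analysis plan that is not shown may analyse unadjusted steps.** It may. The point is not that this analysis is missing. It is that the article fixes one definition and attaches the objective label to it.

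A reader might also infer that the tailored arm will inflate its diary entries, because it alone receives update cards, "sent to participants (in this group only) at 4 weeks and 8 weeks post-baseline". The documents do not show this. The cards are a separate three-item instrument, and all arms keep the same seven-day diary at the same time points.

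Nor does any section give steps the task of checking the self-reported primary outcomes, so it would go too far to say that the plan defeats a purpose it states, or that the step result cannot corroborate anything. Most of the definition is still the pedometer count.

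**Conclusion.** The point holds as a conflict between definition and label on one secondary outcome. The step total includes converted participant reports, while the article presents steps as objective. Among unblinded participants, differential reporting of non-ambulatory activity would pass directly into the step comparison.

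The size cannot be derived. The illustrative 210 to 860 steps/day, or 11% to 43% of the 2000-step target, rests wholly on the assumed conversion rate and the assumed difference in reported minutes. The direction is also unknown, since no section establishes that one arm would report more fully than another. The primary outcomes, sample size and randomisation are unaffected.

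**What to change.** Prespecify and report two between-group analyses of steps: unadjusted pedometer steps, and steps with the equivalents added. Base any statement about an objective effect on physical activity, including those in Statistical power and sample size and in the Discussion, on the unadjusted steps. Acknowledge that participants transcribe these counts themselves.

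The cost is one further analysis of a secondary outcome. No new data are needed, since the pedometer count and the reported activity are both recorded in the same diary. The small downside is that unadjusted steps miss swimming and cycling. The adjusted total, reported beside them, shows what is missed and how far the conclusion depends on the conversion.
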